##### Subjective cognitive complaints

2.4.3.4

Subjective cognitive complaints will be assessed using the *Complainer Profile Identification questionnaire* (CPI) (Lubitz et al., 2018). The CPI comprises 17 items rated on a 5-point frequency scale (“never” to “very often”) and differentiates complaints across the three domains memory, executive function and attention, which can also be presented separately. Previous work shows that SCCs are strongly influenced by affective symptoms and psychosocial factors (Reid and MacLullich, 2006; Smit et al., 2024), and do not necessarily align with objective cognitive performance (Slavin et al., 2010). Including the CPI and the FEDA therefore enables investigation of whether EEG-based markers of sustained attention are more closely related to objective performance or to perceived cognitive difficulties.

#### Electroencephalography

2.4.4

EEG will be recorded in a laboratory environment to reduce and standardize external influences, such as light and noise. We will record EEG using a 32-channel layout connected to an actiChamp amplifier (BrainVision Brain Products GmbH). Electrodes will be placed according to the 10–20 system and online data collection will be done with an amplitude resolution of 0.1 μV and a sampling rate of 500 Hz, with online filters of 0.016–250 Hz. We aim for electrode impedances below 15 kΩ. EOG activity will be recorded using a single dedicated EOG electrode, placed below the left eye. Data will be recorded via the LSL protocol using the Lab Recorder (Kothe et al., 2024). Frequency bands will be analyzed during a subsequent 10-min resting period, divided into 5 min with eyes closed and 5 min with eyes open.

### Data analysis and statistical approaches

2.5

Non-time series data, such as questionnaires, will be partially digitally collected and managed using the Research Electronic Data Capture (REDCap) tool hosted at the University of Kiel (Harris et al., 2009; Harris et al., 2019). REDCap is a secure, web-based software platform designed to support data capture for research studies, providing (1) an intuitive interface for validated data capture; (2) audit trails for tracking data manipulation and export procedures; (3) automated export procedures for seamless data downloads to common statistical packages; and (4) procedures for data integration and interoperability with external sources. Statistical analyses will be performed using JASP (currently Version 0.18.3) (JASP Team, 2024). We will use common descriptive and inferential statistics, as well as appropriate non-parametric statistics, to summarize the baseline data (Fortenbaugh et al., 2015). We will test for normality with Shapiro-Wilk test and Q–Q plots. To assess time-on-task effects, paired *t*-tests or Wilcoxon signed-rank tests will be used to compare reaction times and errors between the first and last quarters of the tasks (Pershin et al., 2023). In addition, correlation analyses (Pearson or Spearman) will be performed to assess the relationship between the number of trials and reaction time. Multiple linear regression will be used to analyze the influence of confounding factors (e.g., age, gender, depression, and cognitive function) on task scores.

Paired *t*-tests or Wilcoxon signed-rank tests will be used for pre-post comparisons to detect changes in clinical variables, as well as behavioral and EEG measures of sustained attention.

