**Methods/design:**

The study “Studying Neurocognitive Systems for Sustained Attention in Neurogeriatrics Patients” (SENSE-AGE) is a prospective, explorative, observational study and will include 120 geriatric participants. At admission, participants will perform a Go-NoGo task, a Psychomotor Vigilance Task (PVT) and resting-state condition during EEG recording, using a 32-channel system. Task-based event-related potentials (ERPs) and frequency-band power will be extracted. Neuropsychological tests characterize global and domain-specific cognition and will examine associations between sustained attention, broader cognitive performance, and EEG parameters. Questionnaires will assess fatigue, sleep, health-related quality of life, and subjective cognition. A subgroup of 50 participants will be re-evaluated at the end of the inpatient stay, after 2–3 weeks of standardized geriatric complex treatment. The main hypotheses of the study are: sustained attention (i) correlates with ERP amplitude and latency; (ii) correlates with EEG power; (iii) improves after an inpatient multiprofessional complex treatment at both the task-performance and neurophysiological level.

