Sustained attention will be measured with a 16-min cued Go-NoGo task on a computer [adapted from Pershin et al. (2023)]. Participants will see different pairs of pictures from the categories “animals,” “trees” and “fruits” (see Table 1) and have to react as fast as possible by pressing a button when two pictures with animals are shown (Go condition). In the NoGo condition, participants will see an animal as the first stimulus and a tree as the second stimulus, and have to inhibit their response (see Figure 3). The Ignore and Ignore & Novelty conditions will show two trees in a row or a tree and a fruit. No response will be required in these conditions. The presentation duration (100 ms), the interstimulus interval (1,000 ms) and the inter-trial interval will be controlled and the stimulus presentation will be randomized. Sustained attention performance in the Go-NoGo task will be quantified using several behavioral parameters. Median reaction time (RT) for correct responses in Go trials will serve as an index of sustained attentional performance. In addition, omission errors (failure to respond to Go stimuli, calculated as the proportion of missed Go trials) will be analyzed as indicators of attentional lapses, and commission errors (responses during NoGo trials, calculated as the proportion of false responses) as indicator of inhibitory control failures. Furthermore, discriminability (*d*’) will be calculated based on signal detection theory [*d*’ = Z(hit rate) – Z(false alarm rate)] to provide a bias-independent measure of sustained attention performance (Fortenbaugh et al., 2015).

**TABLE 1 T1:** The four different conditions of the Go-NoGo task.

Condition	Stimulus 1	Stimulus 2
Go	Animal	Animal
NoGo	Animal	Tree
Ignore	Tree	Tree
Ignore and novelty	Tree	Fruit

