### Limitations due to missing control group

3.1

The absence of a control group precludes any conclusion regarding the extent of sustained attention deficits due to mere age-related changes in sustained attention. In addition, several practical challenges may arise when implementing EEG protocols in a neurogeriatric inpatient population. Increased movement, tremor, reduced tolerance for prolonged testing, and medication effects may introduce variability into electrophysiological measures. Fatigue-related fluctuations during the computerized sustained attention tasks may also differentially affect early vs. late task phases. The clinical heterogeneity of the cohort, while increasing ecological validity, may lead to increased variance and reduced statistical power for specific subgroup effects. Moreover, the observational design limits the interpretability of results concerning potential causal inference between sustained attention, EEG parameters, and psychosocial variables.

For the subsample of participants who will be measured twice, the absence of a control group precludes a definitive conclusion regarding the extent to which any observed changes over the study period can be attributed to the complex geriatric treatment, as opposed to other potential influences, such as an extended stay in hospital or care facility in general. Additionally, even considering the generally good retest reliabilities of resting-state and task-based EEG measures, it will not be possible to causally attribute the observed changes in ERPs or power to the treatment of the participants (Näpflin et al., 2008; Vázquez-Marrufo et al., 2020; Popov et al., 2023).

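### The supplementary correlation of trial number with reaction time has no stated unit of analysis, and two of its three readings give an invalid p-value

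*Protocol article*

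**What the plan says.** Section 2.5 (Data analysis and statistical approaches) gives two analyses of time-on-task.

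- Named first: paired t-tests or "Wilcoxon signed-rank tests will be used to compare reaction times and errors between the first and last quarters of the tasks".
- Named as an addition: "correlation analyses (Pearson or Spearman) will be performed to assess the relationship between the number of trials and reaction time".

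For the correlation, the article names no per-patient summary step, mixed model or other handling of repeated trials. The abstract says that the study "will include 120 geriatric participants". On the task, section 2.4.2 says: "Sustained attention will be measured with a 16-min cued Go-NoGo task on a computer". The number of Go trials is not given. Section 3.1 expects patients to differ: "The clinical heterogeneity of the cohort, while increasing ecological validity, may lead to increased variance", and "Fatigue-related fluctuations during the computerized sustained attention tasks may also differentially affect early vs. late task phases". No significance level or power is stated for this analysis.

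**The concern.** Reaction times from successive trials of one patient are repeated measures. Pearson and Spearman p-values assume independent pairs. Whether that holds here depends on how the trials are combined, and the sentence allows three ways:

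1. **Pooled.** All trials of all patients form one sample. Differences between patients in mean reaction time inflate the residual variance, which makes the test too cautious. Differences between patients in slowing add variance that the formula ignores, which makes it too liberal.
2. **Trial means.** Reaction time is averaged over patients at each trial position and then correlated with position. Trials become the sampling unit, so variation in slope between patients is not counted at all.
3. **Per patient.** One correlation is computed per patient, and these are tested across patients. This is valid.

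At stake is the p-value for a mean slowing over the task. Research question (ii) asks whether associations with EEG power differ between early or late task phases and the whole task, so readers will look at the behavioural decrement as context.

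**Working it through.** **No figure to reproduce.** The article states no error rate, power or effect size for this analysis. The check is therefore the type I error of each reading under assumed values.

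**Inputs**

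- Patients: N = 120 (abstract).
- Assumed, not in the article: m = 80 equally spaced Go trials, all usable, in every patient; between-patient SD σ_b = 100 ms; residual SD σ = 150 ms; SD of the individual change from first to last trial τ = 0, 40, 80 or 120 ms; mean change zero; two-sided level 5%.

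**Formulas.** Scale trial position t from −0.5 to 0.5. Then S = Σt² = m(m+1) / [12(m−1)] = 80 × 81 / (12 × 79) = 6.835.

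- True variance of the mean slope: τ²/N + σ²/(N·S).
- Variance that the pooled correlation assumes: (σ_b² + σ² + τ²S/m)/(N·S).
- Pooled, ratio of true to assumed variance: k = (σ² + τ²S) / (σ_b² + σ² + τ²S/m). Rejection rate = 2[1 − Φ(1.96/√k)].
- Trial means, same ratio: k′ = 1 + τ²S/σ². Rejection rate = P(|t₇₈| > 1.991/√k′).

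**Worked case, τ = 80 ms.** τ²S = 6,400 × 6.835 = 43,744.

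- k = (22,500 + 43,744) / (10,000 + 22,500 + 547) = 66,244 / 33,047 = 2.005. The critical value shrinks to 1.96/√2.005 = 1.384, so the pooled test rejects in 16.6%.
- k′ = 1 + 43,744/22,500 = 2.944. The threshold is 1.991/√2.944 = 1.160, so the trial-mean test rejects in 24.9%.

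**All cases**, with simulation (1,000 runs per row) beside the formula:

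| τ (ms) | k | Pooled, formula | Pooled, simulated | k′ | Trial means, formula | Trial means, simulated |
|---|---|---|---|---|---|---|
| 0 | 0.692 | 1.8% | 1.7% | 1.000 | 5.0% | 4.9% |
| 40 | 1.025 | 5.3% | 4.9% | 1.486 | 10.6% | 9.8% |
| 80 | 2.005 | 16.6% | 15.3% | 2.944 | 24.9% | 22.8% |
| 120 | 3.585 | 30.1% | 30.2% | 5.375 | 39.3% | 40.7% |

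In the same simulations, per-patient slopes tested across patients reject in 3.8% to 5.7%, and the paired quarter t-test in 3.8% to 6.0%.

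**Wider range.** A second simulation used 50, 100 or 200 trials, a between-patient share of variance of 0.3 or 0.5, and a slope SD of 0 to 1 residual SD. It gave:

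- pooled Pearson 0.5% to 57.2%, with pooled Spearman close to it;
- trial means 4.3% to 64.0%;
- per-patient Fisher-z correlations 4.1% to 6.6%;
- paired quarters 4.1% to 5.9%.

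**Power when slopes are equal.** For a true slowing of 10 ms over the task and τ = 0, the pooled test has 34% power and per-patient slopes have 50%.

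**The case against.** The strongest reply is that this is a supplementary analysis in an explorative study, reported in a condensed article, and that nothing in the article says trials are pooled. One correlation per patient would be sound, and the full plan may say so. That stands as far as it goes: the fault is an unfixed unit of analysis, not a proven pooled test. It does not remove the point. The article names a plain correlation as the method, and two of the three readings it leaves open are invalid.

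A reader might infer more than the document supports:

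- **That the time-on-task test as a whole has uncontrolled error.** It does not. The comparison of "reaction times and errors between the first and last quarters of the tasks", read naturally as one value per patient and quarter, respects the nesting and holds about 5%.
- **That the error is always inflation.** It is not. Under pooling with equal slopes the test is conservative. The direction depends on a spread of slopes that the article does not quantify.
- **That patients who stop early will drop out of the quarter comparison.** Section 3.1 mentions "reduced tolerance for prolonged testing" as a source of variability in electrophysiological measures. It does not say that patients will abandon the task.
- **That the quarter test wastes half the information.** For a linear trend, its slope variance is 8σ²/m over 0.75² = 14.2σ²/m, against 12σ²/m for all trials. That is 84% efficiency (12/14.2), and variation in slopes between patients narrows the gap further.
- **That the decrement is the protocol's own definition of a sustained attention deficit.** The introduction gives this as the common view of existing theories and then cites work that challenges it. The behavioural decrement is not itself one of the four research questions.

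**Conclusion.** The point holds in limited form. The trial-number correlation is stated without a unit of analysis. If trials are pooled or averaged over patients, its p-value is not valid. Under the 80-trial assumptions its type I error runs from about 2% to 30% (pooled) or 5% to 41% (trial means), against 4% to 6% for per-patient slopes. Trial count, variances, slope spread and the 5% level are all assumptions, so these ranges show how sensitive the test is and do not predict its behaviour in this study. Some spread of slopes is plausible in a cohort that the article itself calls heterogeneous, so equal slopes should not be taken for granted. The paired quarter comparison is unaffected. The change is worth making because it is cheap, but the study's main analyses do not depend on it.

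**What to change.** In section 2.5, replace the correlation with one of these, for each task:

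- a linear mixed model of correct-trial reaction time on trial number, with a random intercept and a random trial slope per patient; or
- a slope or Fisher-z correlation computed within each patient, tested across patients with a one-sample test.

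Keep the paired first-versus-last-quarter comparison as it is. If a correlation is retained, state that it is computed within patients.

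The cost is a change of wording and slightly more analysis work. No new data are needed.

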#### Controlling for confounding variables

2.5.1

To ensure the validity of our findings, we will control for potential confounding variables such as age (Shearer et al., 1989; Mizukami and Katada, 2018; Tröndle et al., 2023), cognitive status (Soikkeli et al., 1991; Baker et al., 2008), medication use (Centorrino et al., 2002; Blume, 2006; Geraedts et al., 2018), and mental disorders, such as depression, anxiety, and mental fatigue (Greco et al., 2021; Lin et al., 2021; Brush et al., 2022). We will perform an analysis of covariance (ANCOVA) to evaluate the effect of cognitive task performance on EEG components, specifically the N200 and P300. The peak amplitudes and latencies of these components will serve as dependent variables, while performance metrics from the PVT and Go-NoGo tasks will serve as independent variables. The model will identify the impact of task performance on EEG outcomes while controlling for the influence of potential confounding variables.

#### EEG preprocessing

2.5.2

EEG data processing will be conducted using MNE (v1.3.1) (Gramfort, 2013) in Python (3.10). To ensure optimal ICA decomposition quality, a copy of the raw data will be high-pass filtered at 1 Hz (FIR, zero-phase), re-referenced to the common average, and used exclusively for ICA fitting. Noisy channels will be identified and interpolated using the PyPREP package (v0.4.2; (Bigdely-Shamlo et al., 2015)), followed by ICA decomposition. Artifactual independent components (e.g., ocular, cardiac, and muscle artifacts) will be identified using the ICLabel classifier (Pion-Tonachini et al., 2019) and confirmed by visual inspection. The resulting ICA weights and the list of excluded components will subsequently be applied to a separate copy of the raw data bandpass filtered at 0.1–30 Hz. This approach preserves slow neural activity below 1 Hz that is relevant to ERP morphology, following the recommendations of Winkler and colleagues (Winkler et al., 2015). The resulting cleaned, bandpass-filtered (0.1–30 Hz) data form the basis for all subsequent ERP and frequency-band analyses.

#### Event-related potentials

2.5.3

This study will examine the relationship between various ERP components and sustained attention, with emphasis on amplitude and latency. Peak measures are defined as the maximum amplitude of a signal within a specified time window, along with the corresponding time point (latency) at which this peak amplitude occurs. Specifically, we will extract peak measures for the N200 and P300 components. The N200 and P300 will be analyzed in the context of the PVT and the Go-NoGo task, focusing on target responses as well as the occurrence of omission and commission errors.

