On the electrophysiological level, the combination of ERP measures (N200, P300) and spectral power analyses allows for a differentiated characterization of neural dynamics associated with sustained attention (Polich, 2007; Clayton et al., 2015; Liu et al., 2020). Given that EEG recordings in older and multimorbid patients are often associated with increased movement-related and physiological artifacts (Urigüen and Garcia-Zapirain, 2015; Geraedts et al., 2018), particular attention will be paid to data quality and preprocessing procedures. Artifact correction using ICA in combination with automated component classification (ICLabel) will be applied, alongside visual inspection, to ensure careful handling of artifact-prone recordings. The integration of behavioral, electrophysiological, clinical, and self-reported measures strengthens construct validity and enables the examination of sustained attention within a clinically meaningful and ecologically valid framework. Important covariates that are known to impact treatment success and quality of life will also be considered. Moreover, in a subgroup, we will examine potential changes in sustained attention performance over 2–3 weeks of complex geriatric treatment.

From an analytical perspective, the study is designed to go beyond descriptive comparisons and to examine associations between behavioral and electrophysiological markers using correlational and multivariate approaches. We expect sustained attention performance indices (e.g., reaction time variability) to correlate with ERP parameters, particularly P300 amplitude and latency, as well as with frontal theta and global alpha power. Multiple regression analyses will allow us to determine whether EEG markers explain variance in sustained attention performance beyond global cognitive status (MoCA), age, and affective symptom burden. Exploratory moderation analyses using regression models with interaction terms will examine whether fatigue, depressive symptoms, or sleep quality influence the relationship between behavioral performance and neural markers. This analytical framework allows differentiation between electrophysiological parameters that reflect sustained attention specifically and those that may represent broader cognitive or affective influences.

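### Peak N200 and P300 measures grow as fewer epochs are averaged, and epoch counts partly follow task performance, so the ERP-performance associations can be created or masked by noise

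*Protocol article*

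**What the plan says.** Section 2.5.3 (Event-related potentials) sets the measurement rule: "Peak measures are defined as the maximum amplitude of a signal within a specified time window, along with the corresponding time point (latency". It then applies that rule to both components: "Specifically, we will extract peak measures for the N200 and P300 components". The ERPs are to be examined in the PVT and the Go-NoGo task, "focusing on target responses as well as the occurrence of omission and commission errors".

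Section 2.5.1 (Controlling for confounding variables) puts the measures into the ANCOVA: "The peak amplitudes and latencies of these components will serve as dependent variables". On the other side of that model stand the behavioural results: "performance metrics from the PVT and Go-NoGo tasks will serve as independent variables". The confounders named there are age, cognitive status, medication and mental disorders.

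Section 2.4.2 (Cognition) defines two of the performance metrics. Omissions are "failure to respond to Go stimuli, calculated as the proportion of missed Go trials" and commissions are "responses during NoGo trials, calculated as the proportion of false responses". The same section adds d', median reaction time on correct Go trials and reaction-time variability.

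The Discussion (section 3) notes that "EEG recordings in older and multimorbid patients are often associated with increased movement-related and physiological artifacts". Its answer is ICA with automated component classification and visual inspection.

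**The concern.** The mean of a time window is a linear function of the averaged signal, so noise leaves its expectation unchanged. A maximum is not linear. It lies at or above the value at the true peak, and the excess grows with the noise left in the average, which falls with the square root of the epoch count.

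If epoch counts were unrelated to performance, this would only add scatter. Here they are related by construction. Each omission removes one epoch from the correct-Go average and raises the omission rate. If error trials are averaged, each error adds an epoch to that average and worsens the performance score. The bias in the dependent variable is therefore tied to the independent variable.

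This bears on the first main hypothesis, that sustained attention correlates with ERP amplitude and latency. The Introduction expects larger P300 amplitudes with better performance. Bias in Go averages works against that relation, and bias in error-trial averages imitates it.

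**Working it through.** The article states no effect size, trial count or noise level, so there is no figure of its own to reproduce. The check is a simulation.

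**Inputs from the article:** 500 Hz sampling (section 2.4.4), 0.1-30 Hz band (section 2.5.2), 120 participants (Abstract).

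**Assumed inputs:** P300 of +6 µV at 400 ms and N200 of -3 µV at 250 ms; 1/f single-trial noise with SD 10 or 15 µV; windows 200-300 ms (N200) and 300-600 ms (P300); between-patient SD 2 µV (P300) and 1 µV (N200).

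**Step 1: residual noise.** Noise SD in an average of n epochs is s/√n. With s = 10 µV this is 10/√80 = 1.12 µV, 10/√20 = 2.24 µV and 10/√5 = 4.47 µV.

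**Step 2: effect on the measures (s = 10 µV).** The true P300 peak is 6.0 µV, the true window mean 3.2 µV and the true N200 trough -2.4 µV.

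| Epochs | P300 peak (µV) | Excess (µV) | P300 window mean (µV) | N200 negative peak (µV) | P300 latency SD (ms) |
|---|---|---|---|---|---|
| 120 | 6.5 | 0.5 | 3.2 | -2.8 | 19 |
| 80 | 6.7 | 0.7 | 3.2 | -2.9 | 22 |
| 40 | 7.1 | 1.1 | 3.2 | -3.2 | 28 |
| 20 | 7.8 | 1.8 | 3.2 | -3.7 | 36 |
| 10 | 8.9 | 2.9 | 3.2 | -4.6 | 49 |
| 5 | 10.5 | 4.5 | 3.2 | -5.8 | 61 |

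Between 80 and 20 epochs the peak gains 7.8 - 6.7 = 1.1 µV, about half the assumed between-patient SD of 2 µV. The window mean does not move.

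**Step 3: spurious correlation.** True amplitude is unrelated to performance, and epoch count follows performance rank exactly. The two-sided 5% limit for n = 120 is |r| > 1.980/√(1.980² + 118) = 0.179.

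| Epochs per patient | P300 peak r | Rejection | N200 peak r | Rejection |
|---|---|---|---|---|
| Go, 60-80 (s = 10) | -0.02 | 6% | -0.03 | 7% |
| Go, 40-80 (s = 10 and 15) | -0.05 to -0.07 | 8-12% | -0.06 to -0.07 | 10-12% |
| Go, 20-80 (s = 10 and 15) | -0.11 to -0.16 | 24-43% | -0.12 to -0.14 | 26-33% |
| Errors, 3-25 (s = 10 and 15) | +0.27 to +0.32 | 86-93% | +0.21 to +0.23 | 65-74% |

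A negative r means larger peaks in poor performers. N200 is taken here as the size of the negative peak. Window-mean amplitude gives r near 0, with rejection of about 5-7% for Go averages and 7-10% for error averages. The small excess in the latter comes from unequal variance.

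**Step 4: second simulation.** A separate run with the same P300 size, noise SD 10 µV and sample size gave peaks from 6.6 µV (120 epochs) to 11.4 µV (5). For 20-80 Go epochs it gave r = -0.15 with 38% rejection, and for 60-80 it gave 6%. For 3-25 error epochs it gave r = +0.36 with 98%. Mean amplitude stayed near r = 0, with 5-8%.

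**Step 5: partial tracking.** If epoch count and performance correlate at 0.5 and not 1, the induced r is about -0.15 × 0.5 = -0.075. With a standard error of about 1/√119 = 0.092, the rejection rate is about Φ(-(0.179 - 0.075)/0.092) = Φ(-1.13) = 13%. The second simulation gave 14%.

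**Step 6: N200 wording.** Read literally, the maximum in the N200 window is positive in about 79-89% of simulated averages. With 80-120 epochs it sits on a window edge in 72-93%. Read as the negative peak, there is no polarity error.

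**The case against.** **Polarity.** A reader might infer that the analysis will pick the wrong polarity for N200. The article does not support that. Its Introduction speaks of higher N2 amplitudes in high performers and of a reduced N200 in older adults, which makes sense only if amplitude means magnitude in the component's own direction. The rule is loosely worded, but the intent is probably the negative peak.

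**Trial loss is assumed.** No trial counts are given. The preprocessing section describes artifact correction, which keeps epochs, and names no epoch-rejection step, so large artifact-driven loss is not documented. Only omissions and d' are tied to the correct-Go count by definition. The link for reaction time, its variability and the PVT metrics is assumed. This stands, and it is why the size is conditional.

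**Error-trial averages are inferred.** The phrase about the occurrence of errors could mean relating ERPs to error rates and not averaging error epochs. This also stands, so the severe case applies only if such averages are formed.

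**Cancelling or reversing a true effect.** A reader might infer that the bias reverses the expected relation, or that poor performers always receive inflated peaks. Neither is shown. No true effect was simulated, and the sign flips between Go and error averages.

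**Detail left to a fuller plan.** Window limits and minimum epoch counts may sit elsewhere, and their absence is not the point. Peak measurement is a choice that the article does state. Fixing the window does not remove the bias, and a minimum count removes it only if set high. The study is also explorative, which lowers the grade but does not remove the bias.

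**Conclusion.** The point holds in conditional form. The stated peak rule, used as the dependent variable against performance, carries a noise bias that is partly tied to the predictor, and the confounders named in section 2.5.1 do not include epoch count.

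- **Nearly all patients keep 60 or more Go epochs:** negligible, with rejection close to nominal.
- **20-80 Go epochs:** moderate, spurious r about -0.08 (half tracking) to -0.15 (full tracking), with larger peaks in poor performers.
- **Averages of few omission or commission trials:** severe, spurious r about +0.2 to +0.4, with larger peaks in good performers.

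Latency is affected through its variance: at noise SD 10 µV its SD rises from 19 ms (120 epochs) to 61 ms (5 epochs). The N200 polarity is a wording correction. All sizes rest on the assumed signal, noise, windows and epoch ranges; the mechanism does not. Grade: should-fix, moderate confidence.

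**What to change.** In sections 2.5.1 and 2.5.3:

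- Make mean amplitude in a pre-set window the main amplitude measure and fractional-area latency the main latency measure.
- Define N200 as negative-going and P300 as positive-going.
- Keep peak measures as a sensitivity analysis, with epoch numbers matched across patients wherever a peak is used.
- Base the performance correlations on correct trials, and label any error-trial ERPs as exploratory.

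The cost is analysis wording and code; no new data are needed. The downside is that mean amplitude depends on the chosen window and is less comparable with studies that report peaks. The peak sensitivity analysis partly covers that.
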